### Outcome evaluation

#### Design

The study is a mixed-methods repeated measures evaluation that uses caregiver and Hub practitioner surveys at baseline, 6 and 12 months after Hub implementation begins and in-depth interviews at 12 months.

#### Participants

We aim to recruit two stakeholder groups: caregivers (n*=*100–200 per site) and Hub practitioners (n=20–30 per site).

##### Caregivers

Potential caregiver participants are those who: (i) care for a child aged 0–8 years, including women who are pregnant, (ii) access any of the universal or specialist services provided in the Hub, such as general practitioners (GPs), paediatricians, lawyers and (iii) can understand written or spoken English language. The English language criterion is a limitation of our study; however, funding is not available to provide interpreters. Furthermore, culturally and linguistically diverse persons participated in an informed and meaningful way in phone-based or in-person surveys for HHAN (personal communication [name]).

Given the preventative focus of this study, caregivers will not be screened for adverse experiences as an inclusion criterion. Instead, caregivers will report the frequency of 15 adversity types in the baseline survey. These adversity types are derived from the Parent Engagement Resource^61^ and include challenges with: social support, finances, housing, employment, family physical health, parent mental health, parenting, child neglect, alcohol and substance use, family relationships, family violence, child abuse, visa and immigration issues, crime issues and discrimination.

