### Study phase 2: testing of initial Hub theory using empirical data

We will empirically test the initial programme theory for the Hubs through a mixed-methods process with 6 and 12 months outcomes evaluation. The evaluation aims to assess for whom, how and why the Hub models had an impact (if any) in the two different contexts of Wyndham Vale and Marrickville across the child, caregiver, practitioner and system level outcomes specified in figures 2 and 3, table 1 and ‘Outcomes Assessment’ below.

**Table 1 T1:** Primary and secondary outcomes

Primary outcomes		Baseline assessment		6 and 12 months post Hub implementation begins	
		**Caregiver survey**	**Practitioner survey**	**Caregiver survey**	**Practitioner survey**
*Caregiver*					
Identification of adversity	Increase in the proportion of caregivers who report being asked by a service provider about adversity in the past 6 months.	X		X	
Intervention for adversity	Increase in the proportion of caregivers who report spending extra time with or receiving an intervention from a Hub service provider for adversity in the past 6 months.	X		X	
Referrals for adversity	Increase in the proportion of caregivers who report receiving a referral to an intersectoral service for adversity in the past 6 months.	X		X	

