**Secondary outcomes**					
*Child*					
Infant temperament	Increase in the proportion of caregivers who report their infant is easier/much easier than average; assessed through single caregiver-reported item on infant temperament; has a moderate correlation (*r*=0.51) with the Easy-Difficult Scale (EDS) of Australian version short form of Revised Infant Temperament Questionnaire^78^; completed for one child* aged 0–8 in each family 0 to <2 years.	X		X	
Child mental health	Decrease in the mean scores for caregiver-reported internalising or externalising symptoms for their child. Completed for one child* in each family. For children aged 0 to <2 years: Ages & Stages Questionnaire Social-Emotional Second Edition (ASQ-SE2).^79^† For children aged ≥2 to 8 years: Strengths & Difficulties Questionnaire.^80^	X		X	
Global health	Increase in the mean scores of caregiver-reported general child health; assessed through single item (GHQ-S1) from Child Health Questionnaire^81^; completed for one child* aged 0–8 in each family.	X		X	
*Caregiver*					
Uptake of referrals	Increase in the proportion of caregivers who report uptake of referrals to other services in the past 6 months.	X		X	
Mental health	Decrease in the mean scores of caregiver-reported psychological distress as assessed by Kessler Psychological Distress Scale 6 (K6); 6-item.^82^	X		X	
Global health	Increase in means scores of caregiver-reported general health; assessed through single item of the Short Form Health Survey (SF-12).^83^	X		X	
Parental warmth, parenting hostility and efficacy	Increase in mean scores of parental warmth and efficacy; decrease in mean scores on parenting hostility. Three self-report subscales drawn from the Longitudinal Study of Australian Children (LSAC), Australia’s first nationally representative longitudinal study of child development which will allow for national comparisons of the study data^84^; assessing parental warmth, parenting hostility and efficacy. Parental warmth (6-items), parenting hostility (5-items) and parenting efficacy (4-items).	X		X	
Quality of life	Increase in mean caregiver quality of life scores calculated from the EuroQol Health and Well-being Instrument Short Form (EQ-HWB-S).^72^	X		X	

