#### Data collection

##### Caregiver and Hub practitioner surveys

The Caregiver and Hub practitioner baseline and outcome surveys consisting of the measures outlined in table 1 and available in online supplemental file 1 will be built in Research Electronic Data Capture (REDCap)^63^ hosted by Murdoch Children’s Research Institute. After completing an informed consent process, caregivers can complete the baseline survey: (i) in paper form, (ii) over the telephone with a researcher or (iii) online. Practitioners will complete the practitioner baseline survey in paper form or online via REDCap. The practitioner survey will be sent towards the end of baseline data collection to minimise the potential impact of the survey on clinical practice prior to the Hub testing period. Caregiver and practitioner participants will be contacted by telephone, email or text message by the research team 6 and 12 months after the Hub implementation begins and invited to complete the follow-up survey.

10.1136/bmjopen-2021-055431.supp1Supplementary data

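### Intervention and referral for adversity are counted over all caregivers, so their change between waves mixes change in need with change in response; referral uptake has a related denominator problem

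*Protocol article*

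**What the plan says.** Table 1 of the Protocol article (under Study phase 2) words the three primary outcomes as follows, each with an increase as the hoped-for direction:

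- Identification: "proportion of caregivers who report being asked by a service provider about adversity in the past 6 months".
- Intervention: "proportion of caregivers who report spending extra time with or receiving an intervention from a Hub service provider for adversity", over the same six-month window.
- Referral: "proportion of caregivers who report receiving a referral to an intersectoral service for adversity in the past 6 months".

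The secondary outcome on uptake is worded "Increase in the proportion of caregivers who report uptake of referrals to other services in the past 6 months". None of these entries limits the denominator to caregivers who have an adversity or, for uptake, to caregivers who were referred.

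The Caregivers section says that "caregivers will not be screened for adverse experiences as an inclusion criterion". In place of screening, "caregivers will report the frequency of 15 adversity types in the baseline survey". It does not say that the list is repeated later, nor that it is dropped. Caregiver and Hub practitioner surveys describes the "baseline and outcome surveys consisting of the measures outlined in table 1 and available in online supplemental file 1". Table 1 has no row for the 15-type list at any wave, and the supplement is not available here.

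Quantitative data analysis examines change in proportions or means between each pair of waves. It states no conditioning on need.

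**The concern.** Someone without an adversity has little to be treated or referred for. In a sample that mixes caregivers with and without need, the share who received an intervention or referral for adversity depends on two things: how many had a need in the window, and how many of those got a response. The study's aim is about the second.

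Caregivers are recruited in waiting rooms and through practitioners (Recruitment and consent), that is, while they are using services. Need at entry may therefore differ from need 6 or 12 months later. If need falls, (ii) and (iii) can fall or stay flat while care improves. If need rises, they can rise with no improvement. An increase is then not a dependable sign of success.

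Whether this can be repaired in the analysis depends on what the follow-up surveys ask. If adversity is not recorded at 6 and 12 months, no later analysis plan can recover it.

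Uptake has a simpler version of the problem. Counted over all caregivers, it combines the chance of being referred with the chance of acting on a referral.

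**Working it through.** **Inputs from the Protocol article.** Denominator for (ii), (iii) and uptake: caregivers, unrestricted (Table 1). Sample not selected on need (Caregivers). Analysis: change between waves (Quantitative data analysis). Size: 100–200 caregivers at each of two sites, so 2 × 100 to 2 × 200 = 200–400, which agrees with the stated total. The article gives no expected rate, effect size, alpha or power, so there is no calculated figure to reproduce.

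**Assumed inputs.** Prevalence of need π between 40% and 60%; response among those in need r of 40% or 60%. The documents give neither, so these values are illustrative.

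**Formula.** If only caregivers with a need can receive something for adversity, the all-caregiver proportion is P = π × r. If some caregivers without a reported need are also counted, the effect of changing need is smaller but has the same direction.

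**Step 1: need changes, response does not.**

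| Need | Response | All-caregiver proportion | Change |
|---|---|---|---|
| 60% → 40% | 40% → 40% | 24% → 16% | −8 points |
| 40% → 60% | 40% → 40% | 16% → 24% | +8 points |
| 60% → 50% | 40% → 40% | 24% → 20% | −4 points |
| 50% → 60% | 40% → 40% | 20% → 24% | +4 points |

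**Step 2: both change.** P is unchanged when the later response equals r₀ × π₀ / π₁. With need falling from 60% to 40%, that is 0.40 × 0.60 / 0.40 = 0.60. A rise in response from 40% to 60% therefore leaves P at 24% at both waves.

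**Step 3: need stable.** With π = 50% at both waves, response rising from 40% to 60% gives P = 20% → 30%. The direction is right, and the 20-point gain shows as 10 points.

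**Step 4: would the artefact be noticed?** For 24% against 16%, with a two-sided 0.05 test and the waves treated as independent, the chance of a significant result is about 0.52 with 200 caregivers per wave and 0.81 with 400. This only gives scale: the article names no test, and repeated measures on the same caregivers are not independent.

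**Step 5: denominator limited to need in the same window.** Unchanged response reads 40% → 40%, and improved response reads 40% → 60%, whatever happens to prevalence. This requires adversity to be recorded at each wave.

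**Step 6: denominator limited to adversity at baseline.** If a share s of these caregivers still has need later, the later proportion is s × r.

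| Need persists in | Unchanged response (40%) | Improved response (60%) |
|---|---|---|
| 50% | 40% → 20% | 40% → 30% |
| 67% | 40% → 27% | 40% → 40% |
| 80% | 40% → 32% | 40% → 48% |

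The baseline record alone is a partial remedy.

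**Step 7: precision with smaller denominators.** If 30–70% of 200–400 caregivers report need, n runs from 0.30 × 200 = 60 to 0.70 × 400 = 280. The 95% half-width at 40% is 1.96 × √(0.4 × 0.6 / n), which is 12.4 points at n = 60 and 5.7 points at n = 280.

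**Step 8: uptake.** Assume half of referrals are taken up throughout. If referrals rise from 20% to 40% of caregivers, uptake over all caregivers goes from 0.20 × 0.50 = 10% to 0.40 × 0.50 = 20%. It doubles although the share taken up has not moved.

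**The case against.** A reader might infer that adversity is recorded only at baseline. The documents do not establish this. The sentence naming the baseline survey explains what replaces screening at entry. Table 1 omits the list even at baseline, so its absence there says nothing about follow-up, and the surveys are in a supplement that is not shown. What stands is that repetition at follow-up is not stated.

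A reader might also infer that the primary outcomes as a whole cannot show response to need. That goes too far in three ways:

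- Identification does not require a need and is properly counted over all caregivers.
- If need is stable, (ii) and (iii) do track response. The adversity types are broad and both areas are of low socioeconomic status, so need could be high and steady. No passage supports a shift of 10 to 20 points.
- Some information on need exists. Health economics analysis separates met, absent and unmet needs, using the ASQ or SDQ. Caregiver distress (K6) is repeated at each wave. Baseline adversity would allow a stratified analysis, although none is stated. These are partial: the child measures do not cover housing, finances or family violence, and need can change after baseline.

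The idea that a Hub which resolves adversity must lower its own outcomes is limited by the six-month recall. A need met within the window can still count as a response. The mechanism therefore bears mainly on the 12-month survey, for needs resolved earlier.

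The lack of a comparison group is an acknowledged limitation, and it covers attribution of secular change. It does not settle what the proportion measures.

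A denominator based on need at the same wave has its own bias. It is measured after Hub exposure, staff training may change what caregivers recognise or disclose, and the subsets differ between waves. This objection stands, and it is a reason not to replace the primary definition.

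Finally, exact denominators are often left to an analysis plan. That is fair for the analysis, but not for a survey item that may not be collected.

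**Conclusion.** The point holds for primary outcomes (ii) and (iii). As worded and analysed, they confound change in need with change in response, and do not reliably show response to need unless need is stable. At an assumed 40% response, a 10-point change in need alone moves them by 4 points and a 20-point change by 8. A rise in response from 40% to 60% is fully hidden if need falls from 60% to 40%. All these rates are assumptions, and the size in this study is unknown. Identification is unaffected.

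Uptake as worded follows the volume of referrals. This needs no assumption about adversity, but it concerns a secondary outcome.

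The documents leave open whether adversity is asked again at follow-up. The matter does not undermine the design, but it should be settled before the follow-up surveys are final, because missing items cannot be recovered afterwards.

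**What to change.** 1. State whether the 15-type adversity block is asked at 6 and 12 months, with the same six-month window as the outcomes. If it is not, add it.
2. Keep the all-caregiver proportions for (ii) and (iii) as primary, and leave identification as it is.
3. Pre-specify two supporting analyses of (ii) and (iii): among caregivers reporting at least one adversity in the same window, and among those with adversity at baseline. Report the prevalence of adversity at each wave beside them.
4. Define uptake among caregivers who report a referral.

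The cost is an existing item block in two follow-up surveys, so a few more minutes for each caregiver, and wider intervals from smaller denominators. The same-window denominator may also shift with disclosure after Hub exposure, which is why it should support the primary result and not replace it.

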##### Hub practitioners

Potential practitioner participants are those who: (i) work in any of the intersectoral services provided as part of each Hub, including GPs, maternal and child health nurses, paediatricians, allied health professionals, social workers, lawyers, and (ii) can understand written or spoken English language.

#### Sample size calculation

As this study is testing the Hub models using a non-experimental design, we have not conducted a formal sample size calculation. However, the sample size of 200–400 caregivers is likely to provide rich data on the primary and secondary outcomes.

#### Recruitment and consent

The study is designed to accommodate a range of participants, many of whom may have complex life circumstances.^62^
Figure 4 presents the caregiver participant study flow. We will recruit caregivers from the waiting rooms of each Hub and through Hub practitioners who will ask their clients’ permission for the research team to contact them. Researchers will approach potential caregiver participants (in the waiting room or on the telephone), show and/or email them an informational video and study information pack (including a written Caregiver Participant Information Consent Form, PICF) and invite them to take part in the study. Participants can provide informed consent verbally on the phone or in-person, or in writing by clicking through the online consent form preceding the survey. Caregivers will be provided with a AUD$25 honorarium for each survey and/or interview they complete.

**Figure 4 F4:**
[figure not shown]
Caregiver participant study flow. PICF, Participant Information Consent Form.

We will invite practitioners working in each Hub who have been identified and recruited by the study team or health centre managers. We will send an invitation email to potential practitioner participants with the Practitioner PICF attached before they attend the workforce training. Practitioner participants will provide written (online or hard copy) informed consent prior to completing the baseline survey.

### Outcome assessment

The study will assess the child, caregiver, practitioner and systems outcomes summarised in table 1.

#### Data collection

##### Caregiver and Hub practitioner surveys

The Caregiver and Hub practitioner baseline and outcome surveys consisting of the measures outlined in table 1 and available in online supplemental file 1 will be built in Research Electronic Data Capture (REDCap)^63^ hosted by Murdoch Children’s Research Institute. After completing an informed consent process, caregivers can complete the baseline survey: (i) in paper form, (ii) over the telephone with a researcher or (iii) online. Practitioners will complete the practitioner baseline survey in paper form or online via REDCap. The practitioner survey will be sent towards the end of baseline data collection to minimise the potential impact of the survey on clinical practice prior to the Hub testing period. Caregiver and practitioner participants will be contacted by telephone, email or text message by the research team 6 and 12 months after the Hub implementation begins and invited to complete the follow-up survey.

10.1136/bmjopen-2021-055431.supp1Supplementary data

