Caregiver experience	Caregiver reported acceptability and feasibility of the Hub; Increase in the proportion of caregivers who report their satisfaction with Hub care as measured by three items from the Australia Bureau of Statistics Patient Experiences in Australia Survey.^85^	X		X	
Personal well-being	Increase in mean scores of caregiver-reported personal well-being outcomes measured by the Personal Well-being Index; 7 items.^86^	X		X	
*Practitioner*					
Identification of adversity	Increase in the proportion of practitioners who report asking about adversity in the past 6 months.		X		X
Intervention for adversity	Increase in the proportion of practitioners who report spending extra time or providing an intervention for adversity in the past 6 months.		X		X
Referrals for adversity	Increase in the proportion of practitioners who report referring caregivers to an intersectoral service for adversity in the past 6 months.		X		X
Practitioner experience	Practitioner reported acceptability and feasibility of the Hub; Increase in the proportion of practitioners who report feeling confident and competent to detect and support families experiencing adversity.		X		X
*System level*					
Strength and structure of intersectoral service linkages	Increase in the number and strength of service linkages between Hub practitioners as assessed through social network analysis (SNA) indicators for network density, degree, centrality and betweenness, and map of linkages between Hub practitioners based on i) contact, (ii) referrals to, (iii) referrals from, and (iv) quality of the relationship.^68–71^		X		X
Health economics outcomes	Costs of implementation of the Hub models, caregiver-reported intersectoral service usage and value of unmet need.	X		X	

*Caregivers with more than one child will respond to questions pertaining to one child in their family based on the child they are most concerned about.

†The ASQ-SE is limited by its design as a screening tool that may not be a sensitive outcome measure. The measure is used in this study because it more directly measures mental health and well-being than the ASQ.

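### Caregivers join because they are using a service but are followed up whether or not they still are, so change in the primary proportions mixes attendance with practice; the contact share should be reported beside them

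*Protocol article*

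**What the plan says.** **Entry.** Under Caregivers, participants are people who "access any of the universal or specialist services provided in the Hub". Under Recruitment and consent: "We will recruit caregivers from the waiting rooms of each Hub and through Hub practitioners". Both routes select on service access around the time of recruitment.

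**Follow-up.** The Design section sets surveys at "baseline, 6 and 12 months after Hub implementation begins", so the clock runs from Hub start and not from the caregiver's own visit. Under Caregiver and Hub practitioner surveys, participants "will be contacted by telephone, email or text message by the research team 6 and 12 months after the Hub implementation begins". No attendance condition is stated.

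**Primary outcomes (Table 1).** All three are proportions of caregivers with a six-month recall. Identification is the "Increase in the proportion of caregivers who report being asked by a service provider about adversity in the past 6 months". Intervention covers extra time with, or "receiving an intervention from a Hub service provider for adversity in the past 6 months". The referral item names no particular referrer.

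**Analysis.** Under Quantitative data analysis, the outcomes are assessed as change in these proportions between each pair of waves. No denominator based on contact is mentioned. There is no comparison group.

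**Data on contact.** The health economics row of Table 1 lists "caregiver-reported intersectoral service usage and value of unmet need" in the caregiver survey at baseline and at both follow-ups.

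**The concern.** A caregiver can report being asked, helped or referred only if a provider was seen in the window. Sampling ties that contact to service use at baseline and leaves it free at follow-up. The protocol also places baseline data collection before the Hub testing period, so the visit that led to recruitment would normally fall outside both follow-up windows.

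Two opposing shifts follow. Caregivers who stop attending stay in the follow-up denominator and pull the proportions down. Caregivers recruited at a first visit may have had little earlier contact to report, which lowers the baseline and makes later waves look better.

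If contact differs between waves, a real gain in practice could be hidden or shown as a fall, and unchanged practice could appear as a gain. No parallel group would reveal this. The stated limitation, that change cannot be credited to the Hub without a comparison group, concerns the cause of an observed change. It does not say that the change may be one of attendance instead of practice.

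**Working it through.** The protocol reports no formal sample size calculation and gives no contact rate or baseline proportion, so there is no figure of its own to reproduce. **Every rate below is an assumption.**

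**Model.** Let *c* be the share of caregivers with a relevant contact in the recall window, and *q* the chance of a positive answer given contact. Then observed proportion = *c* × *q*, and change from baseline (0) to follow-up (1) = *c*₁*q*₁ − *c*₀*q*₀. If practice is constant, this is *q*(*c*₁ − *c*₀), which is not zero unless the contact shares are equal.

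**Contact falls.** Set *q* = 0.40 and *c*₀ = 1.
- *c*₁ = 0.90: 0.40 × 0.90 = 0.36, change -4 points.
- *c*₁ = 0.70: 0.40 × 0.70 = 0.28, change -12 points.
- *c*₁ = 0.50: 0.40 × 0.50 = 0.20, change -20 points.

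**First-time attenders at baseline.** A fraction *f* has no earlier relevant contact, with full contact at follow-up. Baseline is 0.40(1 − *f*), so the artefact is 0.40*f*.
- *f* = 0.10: +4 points.
- *f* = 0.30: +12 points.

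**Both at once, *q* = 0.40.**
- *c*₀ = 0.60, *c*₁ = 0.90: 24% to 36%, +12 points.
- *c*₀ = *c*₁ = 0.80: 32% to 32%, no artefact.
- *c*₀ = 0.90, *c*₁ = 0.60: 36% to 24%, -12 points.

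**Effect on a real improvement.** Let *q* rise from 0.40 to 0.50 with *c*₀ = 1.
- *c*₁ = 0.90: 0.45 − 0.40 = +5 points.
- *c*₁ = 0.80: 0.40 − 0.40 = 0.
- *c*₁ = 0.70: 0.35 − 0.40 = -5 points.

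Among caregivers with contact, the same improvement shows as +10 points at any contact level, provided *q* does not depend on who keeps attending.

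**Visibility against sampling error.** The artefactual fall from 40% to 28% would reach two-sided significance at 0.05 with probability about 0.43, 0.72 and 0.95 for n = 100, 200 and 400, the planned per-site and total sizes before attrition. This treats the waves as independent samples, which a repeated-measures cohort is not, so it is only a rough guide.

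**Which items are exposed.** For intervention, *c* is contact with a Hub provider. For identification, Table 1 accepts any service provider, so *c* is at least as large, and the referral item is similarly open. The lower values of *c* are therefore most relevant to intervention. The objectives section attributes all three outcomes to Hub practitioners, so the provider intended for each item needs to be settled before contact is defined.

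**The case against.** The strongest reply is that attendance is partly what the Hub is meant to change. The Introduction presents low service use as the problem and ongoing engagement as a benefit of integrated care. The Hub components include community partnerships, open entry and care navigation, and the logic model expects greater uptake. A Hub that loses its families has not detected their adversity, so a whole-cohort proportion is a defensible measure of reach. Restricting to caregivers with contact conditions on something the Hub may affect. This stands, and it is why the contact-based proportion should not replace the whole-cohort one.

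A reader might also infer that caregivers without Hub contact, and first-time attenders at baseline, must score no. The documents do not support that in general. Under Table 1, another provider can satisfy identification or referral, and the baseline survey can be completed by telephone or online, possibly after the visit. The claim comes close to holding only for the intervention item.

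It is also fair that all the magnitudes are assumed and that the two artefacts oppose each other. The caregiver flow figure and the survey supplement are not shown and could contain a contact filter. Routine attendance data and interviews across levels of engagement will give some context.

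What remains is that the visible text selects baseline on service access, does not do so at follow-up, and compares the waves without separating contact from practice.

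**Conclusion.** The point holds in a limited form. The primary proportions combine provider contact with what happens given contact, and their change can reflect either. The exposure is greatest for the intervention item.

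The net direction and size cannot be derived. The ranges of -20 to -4 and +4 to +12 points rest on an assumed 40% chance given contact and on assumed contact shares, with full contact at the other wave in each case. If contact is similar at all waves, the artefact vanishes.

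A reader might conclude that the primary outcomes are invalid, that the Hub is bound to show a decline, or that contact-conditional proportions must become the sole primary. The documents support none of these: no contact rates are given, the shifts run both ways, and engagement is partly a Hub aim. This is a cheap improvement to interpretation and no bar to proceeding.

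**What to change.** Keep the whole-cohort proportion as a reach-inclusive measure. Beside it, at baseline, 6 and 12 months, pre-specify:

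- (a) the share of caregivers with at least one relevant contact in the six-month window;
- (b) each primary proportion among those caregivers.

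Define relevant contact to match each item's provider wording: a Hub provider (at baseline, the services that make up the Hub) for intervention, and any qualifying provider for identification and referral unless those items are reworded. Derive contact from the service-usage items already planned at each wave. First check that their recall window and provider list allow this, preferably before the surveys are fielded, because past contact is hard to reconstruct later.

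The cost is some analysis wording and an item check. The price is smaller denominators for (b) and some selection, since contact may itself respond to the Hub. For that reason (b) should be read alongside (a) and the whole-cohort result and should not replace it.
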